### Trial design {8}

This is a cluster randomized controlled trial, parallel-group type, where the YSLQQ program is compared to standard school prevention curricula in control schools. The standard school drug prevention curricula are delivered in the orientation class, henceforth “Treatment-As-Usual” (TAU) [23], and it will be used as a comparator to determine the superiority of YSLQQ over TAU in Chile. The patient allocation is randomized with a ratio of 1:1.

## Methods: Participants, interventions, and outcomes

### Study setting {9}

This trial will be performed in primary schools located in Santiago, Chile.

### Eligibility criteria {10}

#### Inclusion criteria for schools

Schools located in Santiago (Chile)Schools having primary education (1st grade to 8th grade)Mixed-sex schools.Schools having at least two classes in the 6th and 7th grades.Schools with medium-high to high vulnerability (≥50%), measured with the School Vulnerability Index – National System of Equality Allocation (IVE-SINAE). This index is the proportion of students in a given school who have high vulnerability. This index considers the following socioeconomic variables to group the schools: mother’s educational level, father’s educational level, total monthly household income, among others [24].

#### Exclusion criteria for schools

Schools having other manualized interventions for substance use prevention targeting the same grades.

#### Inclusion criteria for participants

Attending 6th or 7th grade.

### Who will take informed consent? {26a}

Schools will be screened for eligibility to participate in this study based on the above-mentioned criteria. After the schools have been assessed as eligible by research assistants, the principal of the selected schools will receive study information. After the school authorities accept to participate in the study and sign a form, parents of students will be informed about the study and that the YSLQQ program will be part of the school curriculum sending information letters to their homes. Along with this information, the parent will receive the Informed Consent Form, and they need to sign it if they agree that their children participate in the study. Finally, the students will be informed about the study by research assistants and will be asked to sign an assent confirming their participation.

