**Methods:**

This is a cluster randomized controlled trial, parallel-group type, where “Yo Sé Lo Que Quiero” is compared to standard school preventive curricula in control schools. A total of 70 schools and 8400 adolescents are expected to be randomized with 1:1 allocation. During formative work, the Unplugged program was culturally adapted to Chile, and the instrument to assess the primary and secondary outcomes was validated. The effectiveness of this program will be assessed using the European Drug Addiction Prevention Trial Questionnaire (EU-Dap), measuring substance use prevalence and risk and protective factors in baseline, post-intervention, and four months after the end of the intervention.

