## Interventions

### Explanation for the choice of comparators {6b}

The control group receives the standard school drug prevention curricula (“Treatment-As-Usual”, TAU) [23], which is not a manualized intervention. The standard curriculum includes a class called “Orientation” where students usually participate every week in a class where they receive teaching on health promotion and substance use preventive messages. Most of the material used in these classes comes from state agencies, such as the Ministry of Education and the National Service for the Prevention and Rehabilitation of Drug and Alcohol Abuse (SENDA). Moreover, the curriculum of this class usually does not follow a manualized intervention such as YSLQQ; therefore, we chose the usual orientation class as a treatment-as-usual comparator to determine the superiority of YSLQQ over the common practice in Chile.

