## Assignment of interventions: allocation

Randomization will be performed once all schools are recruited. Schools will be randomly assigned to either group with a 1:1 allocation by computer-generated randomization.

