### Concealment mechanism {16b}

After the randomization and allocation, schools will be informed by a research assistant of the group of belonging by email and confirmed by telephone. Each school will only receive their information of allocation. Additionally, this information will not be disclosed to the assessment research team (outcome evaluators) to keep the blind to the schools’ allocation.

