### Procedure for unblinding if needed {17b}

The design is open label with only outcome assessors and data analysts being blinded so unblinding will not occur. On the other hand, due to the nature of the intervention, the participants will know the allocation of the school.

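### The parent letter describes only the intervention arm, and the readable text does not say that consent, assent and baseline come before allocation

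*Protocol article*

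**What the plan says.** All references are to the Protocol article.

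- **Consent {26a}.** Parents are approached once the school has signed: "After the school authorities accept to participate in the study and sign a form". They are then told about the study, and the section continues: "parents of students will be informed about the study and that the YSLQQ program will be part of the school curriculum". Consent is opt-in: "Along with this information, the parent will receive the Informed Consent Form, and they need to sign it if they agree". Student assent comes last. The section describes neither a separate letter for control schools nor conditional wording.
- **Comparators {6b}.** "The control group receives the standard school drug prevention curricula". Control schools do not receive YSLQQ.
- **Allocation and sequence generation {16a}.** Both give one condition: "Randomization will be performed once all schools are recruited".
- **Concealment {16b}.** "After the randomization and allocation, schools will be informed by a research assistant of the group of belonging by email and confirmed by telephone". Nothing there makes disclosure wait for consent or baseline.
- **Abstract, Methods.** The questionnaire is given three times, "measuring substance use prevalence and risk and protective factors in baseline, post-intervention, and four months after the end of the intervention". Baseline is not placed relative to allocation.
- **Participant timeline {13}.** The section refers to Table 1, a SPIRIT diagram, which was not readable in the copy reviewed.
- **Statistical methods {20a}.** Odds ratios come from a multilevel model that controls for the baseline outcome, on an intention-to-treat basis.

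**The concern.** Randomizing schools makes the arms comparable at school level. It makes the analysed students comparable only if they enter the study without knowledge of the arm. Here a parent's signature decides whether a child is surveyed, and so whether the child can be analysed. If the signature is sought after the arm is known, families in the two arms may opt in differently. This is the usual recruitment bias of cluster trials.

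The planned analysis would repair it only in part:

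- Intention-to-treat covers only students who entered.
- Multiple imputation cannot recover children who never consented.
- Adjustment for the baseline outcome acts on selection by current use. It does not act on selection by future risk, which matters because the stated hypothesis includes initiation of use.
- If the baseline questionnaire is completed after schools know their arm, the adjustment variable is itself exposed.

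Apart from bias, a letter that announces YSLQQ to control families is inaccurate.

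**Working it through.** **1. The two possible orders**

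The consent section says what parents are told, and the comparator section says what control schools get. Together they leave two cases.

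| Order | Letter | Consequence |
|---|---|---|
| Letter after allocation | Can be fitted to the arm | Families consent knowing the arm, so consenting samples can differ by arm |
| Letter before allocation | Same in all schools | Control families are told something untrue of their school; the letter alone creates no difference between arms |

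The text does not settle which case applies. School recruitment ends with the school's signed form, and parental consent comes after that form. Randomization also comes after school recruitment. Nothing readable orders these two later steps. The Trial status section (recruitment from September 2021 to about March 2022) does not settle it either.

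**2. The plan's own figures**

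The illustration below uses the control prevalence and target from the Sample size section, so I first checked that they reproduce the stated size. Inputs: 4.18% against 2.18%, two-sided alpha 0.05, power 0.80, ICC 0.02, and 8400/70 = 120 students per school.

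- Two proportions, no continuity correction: 1208 per arm.
- Design effect: 1 + (120 − 1) × 0.02 = 3.38.
- 1208 × 3.38 = 4083 per arm; 4083/120 = 34.03, so 35 schools, and 35 × 120 = 4200.

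This agrees with 4200 students and 35 schools per arm. The sample size is not in question here.

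**3. How large the bias could be if letters follow allocation**

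The protocol gives no parental consent rate; its 40% refusal allowance concerns schools. The consent rates below are therefore assumptions. There is no true effect, and prevalence is p = 0.0418 in both arms. In intervention schools, users are consented at rate c_u and others at c_n. In control schools there is no such gap, so that arm shows 4.18%.

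Observed prevalence = p·c_u / [p·c_u + (1 − p)·c_n]

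- c_u = 0.60, c_n = 0.70: 0.02508 / (0.02508 + 0.67074) = 3.60%. Spurious reduction 0.58 points, or 29% of the 2-point target.
- c_u = 0.50, c_n = 0.70: 0.02090 / (0.02090 + 0.67074) = 3.02%. Spurious reduction 1.16 points, or 58% of the target.

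On the odds-ratio scale the bias equals c_u/c_n, so 0.60/0.70 = 0.86 and 0.50/0.70 = 0.71. The planned effect corresponds to (0.0218/0.9782)/(0.0418/0.9582) = 0.51.

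These figures are before adjustment for baseline use, which acts directly on the selection modelled here. How much would remain cannot be computed from the documents.

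**The case against.** **Table 1 may give the order.** A SPIRIT diagram is the natural place to show enrolment, baseline and allocation in sequence. A reader might infer that nothing in the plan puts consent and baseline before allocation. The documents do not support that, because the diagram could not be read. This objection stands: the point is limited to the readable text.

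**The letter itself is not shown.** The consent section summarises it in one clause, alongside information about the study, so the letter may explain assignment by lot. That is possible, and an article condenses. Still, the one piece of content the article singles out is untrue for control schools, and that sentence needs correcting in any case.

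**Bias arises in only one of the two cases.** This also stands. A reader might infer that the consenting samples will differ by arm; that requires letters to follow allocation, which the text does not establish.

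**Participants' knowledge of allocation.** The unblinding section {17b} says "due to the nature of the intervention, the participants will know the allocation of the school". A reader might take this to mean that families know the arm when they sign. It does not say so: it is true of any open classroom programme once delivered, and gives no time.

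**Families cannot gain or avoid the programme by signing.** Under {11b}, students in intervention schools attend all sessions whether or not they are in the study. Consent governs the use of data, and the questionnaire is the same in both arms. This weakens the incentive for consent to depend on arm, but does not remove it, since willingness to report a child's substance use may still change once the school is running a prevention programme.

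**The magnitude is assumed.** Correct. It shows only that, with an outcome near 4%, moderate consent gaps are not small beside a 2-point target.

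**Conclusion.** The point holds in limited form. The consent section describes parent information that fits only intervention schools, and the readable text makes randomization and disclosure of arm wait for school recruitment alone. As written, the procedure either allows families to consent knowing the arm or misinforms control families. Both call for correction, but only the first threatens the treatment comparison.

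The possible bias is conditional and cannot be sized from the documents. Assumed gaps of 10 to 20 percentage points, confined to users in intervention schools, give about 0.6 to 1.2 points before baseline adjustment, which would remove part of it. If Table 1 places consent, assent and baseline before allocation, the recruitment-bias part falls away, and what remains is the inaccurate description of the letter and the need to bring the text into line with the diagram.

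This is a cheap improvement of moderate severity. It does not show that the planned comparison is biased.

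**What to change.** 1. **Consent {26a}:** use one arm-neutral letter in all schools, for example: *Your child's school will be assigned by lot either to YSLQQ or to its usual orientation class.* Remove the unconditional statement about the curriculum.
2. **Allocation, sequence generation {16a} and concealment {16b}:** state that allocation is generated, or at least released to schools and the field team, only after parental consent, student assent and the baseline questionnaire are complete in all schools.
3. **Table 1:** check that it shows the same order, and reconcile it with the text.
4. **Reporting:** give parental consent rates by arm, so that readers can judge whether entry differed.

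The cost is protocol and letter wording plus a resequenced calendar; the sample size and model do not change. The downside is that schools learn their arm later, which shortens the window for the 3-day teacher training. The change has to be made before letters go out, because analysis cannot fully correct a sample selected with knowledge of the arm.

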### Additional consent provisions for collection and use of participant data and biological specimens {26b}

Not applicable. No biological samples were collected.

## Interventions

### Explanation for the choice of comparators {6b}

The control group receives the standard school drug prevention curricula (“Treatment-As-Usual”, TAU) [23], which is not a manualized intervention. The standard curriculum includes a class called “Orientation” where students usually participate every week in a class where they receive teaching on health promotion and substance use preventive messages. Most of the material used in these classes comes from state agencies, such as the Ministry of Education and the National Service for the Prevention and Rehabilitation of Drug and Alcohol Abuse (SENDA). Moreover, the curriculum of this class usually does not follow a manualized intervention such as YSLQQ; therefore, we chose the usual orientation class as a treatment-as-usual comparator to determine the superiority of YSLQQ over the common practice in Chile.

### Intervention description {11a}

The intervention group will receive the “Yo Sé Lo Que Quiero” program. This program will be implemented during the academic year during school hours, mainly in the “Orientation” class. It has 12 1-h sessions taught once a week by teachers previously trained in a 3-day course. These 45-min 12 sessions are divided into three themes: (1) Knowledge and attitudes (sessions 1, 3, 5, and 9): students reflect on their knowledge of legal and illegal drugs, using tests to reach an objective assessment of this knowledge; (2) Intrapersonal skills (sessions 4, 6, 8, 10, 11, and 12): students reflect on normative beliefs, where perceived prevalence of drug use at students' age is compared with the actual local prevalence; and (3) Interpersonal skills (sessions 2 and 7): students are instructed to practice refusal skills, assertiveness, and analyze coping strategies. They also are instructed and practiced how to make decisions using a five-step model.

### Criteria for discontinuing or modifying allocated interventions {11b}

Students in the intervention group, as the program is part of the school curriculum, will participate in all sessions of the program. Even though they cannot leave the classroom if they do not want to participate in the sessions, they can leave the study at any time for any reason if they wish to do so without any consequences. This means that their information and collected data will not be analyzed. On the other hand, the control group will keep its condition during the whole trial.

### Strategies to improve adherence to interventions {11c}

Adherence to the “Yo Sé Lo Que Quiero” will be monitored by research assistants from the research team. Teachers will fill out a survey after each session informing the attendance of students and information about the quality of the delivery. Research assistants will be in close contact with school authorities and teachers, monitoring the progression of the program during study visits.

### Relevant concomitant care permitted or prohibited during the trial {11d}

The exclusion criterion states that manualized substance use prevention programs cannot be implemented in control schools. The aim of this study is to test the effectiveness of YSLQQ over TAU in Chile, and the common practice is not the implementation of manualized programs, as stated above in section [3].

### Provisions for post-trial care {30}

There is no potential harm or damage in this trial. The intervention group will receive an evidence-based intervention, and the control group will receive the usual prevention curriculum.

### Outcomes {12}

#### Primary outcome

Regular alcohol use measured with the European Drug Addiction Prevention Trial Questionnaire (EU-Dap) validated in Chile (manuscript under revision). Regular alcohol use is defined as the prevalence of any alcohol use during the last 30 days previous to the survey.

#### Secondary outcomes

Prevalence of substance use:Tobacco use: Tobacco use will be evaluated with two variables: 12-month tobacco use prevalence and 30-day tobacco use prevalence.Alcohol heavy use: Drunkenness will be evaluated with two variables: 12-month drunkenness prevalence and 30-day drunkenness prevalence.Marijuana: Marijuana use will be evaluated with two variables: 12-month marijuana use prevalence and 30-day marijuana use prevalence.(2)Knowledge and skills promoted by the YSLQQ program:Positive and negative beliefs about tobacco use (no. of items = 8, e.g., How likely is that each of the following would happen to you if you smoke cigarettes in the next month? (v) Feel more relaxed; Answers 1= *Very unlikely* to 4= *Very likely*)Positive and negative beliefs about alcohol use (no. of items = 10, e.g., How likely is that each of the following would happen to you if you drink alcohol in the next month? (i) Do badly in school; Answers 1= *Very unlikely* to 4= *Very likely*).Positive and negative beliefs about marijuana use (no. of items = 10, e.g., How likely is that each of the following would happen to you if you take marijuana in the next month? (vi) Have more fun; Answers 1= *Very unlikely* to 4= *Very likely*).Positive and negative attitudes towards drugs (no. of items = 11, e.g., Here are some statements that people have made about illegal substances. How much do you agree with the following opinions on drugs? (iii) Using drugs is fun; Answers 1= *Strongly disagree* to 4= *Strongly agree*).Knowledge about substances (no. of items = 6, e.g. (i) Nicotine is the substance in cigarettes that causes lung cancer; Answers 1= *Yes*, 2= *No, 3= Don’t know*).Normative beliefs [perception of the number of user friends] (no. of items = 5, e.g., When you answer this question, think about the friends with whom you spend most of your leisure time. (iv) How many of them get drunk?; Answers 1= *None* to 5= *All of them*).Refusal skills (no. of items = 3, e.g. (i) You and your best friend are at a party where you meet new people, and you feel you really want to get to know them. Someone offers you to smoke hash together. Your friend accepts. Do you?; Answers 1= *Very unlikely* to 4= *Very likely*).School bonding (no. of items = 5, e.g., How much do you agree with the following descriptions of your school? (i) The students in my class enjoy being together; Answers 1= *Strongly disagree* to 4= *Strongly agree*).Decision-making skills (n. of items = 5, e.g., There are several possible ways to make decisions. How well do the following apply to you? (iv) I often regret something that I had decided; Answers 1= *Strongly disagree* to 4= *Strongly agree*).

### Participant timeline {13}

Table 1 shows the participant’s timeline.

**Table 1 Tab1:**
[figure not shown]
Standard Protocol Items: Recommendations for Interventional Trials (SPIRIT) diagram

### Sample size {14}

Assuming alpha 0.05 (two-sided), power 0.80, with a prevalence of regular alcohol use in the control arm of 4.18% (data available from a secondary analysis of Fourth National Survey of Violence in School Context 2014, which included this information for 7th and 8th graders), and assuming an Absolute Risk Reduction (ARR) of 2% in favor of the intervention group (38), 30 students per class, and Intraclass Correlation (ICC) of 0.02 (54), the estimated sample size is 4200 students per arm, corresponding to 35 schools in the intervention and 35 schools in the control group. Considering a potential refusal to participate of 40%, 120 schools fulfilling the inclusion criteria will be invited to participate. We used the “clustersampsi” command in Stata Software estimating the number of clusters and students in two arms, using the following command:

Clustersampsi, binomial samplesize p1 (X1) p2 (X2) m(y) rho(R)

where X1 = prevalence of regular alcohol use in arm 1, X2 = prevalence of regular alcohol use in arm 2, Y = number of children per school on average, and R = intracluster correlation. Finally, the two arms will be balanced to school size.

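### The sample size allows for schools that refuse but not for students who are not analysed, so the 80% power holds only if student loss stays under about 9%

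*Protocol article*

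**What the plan says.** Section {14} of the protocol gives a complete calculation. The error rates are set by "Assuming alpha 0.05 (two-sided), power 0.80". The outcome assumptions are a "prevalence of regular alcohol use in the control arm of 4.18" per cent, and then "assuming an Absolute Risk Reduction (ARR) of 2% in favor of the intervention group". The clustering inputs are "30 students per class, and Intraclass Correlation (ICC) of 0.02". The result is "the estimated sample size is 4200 students per arm, corresponding to 35 schools in the intervention and 35 schools in the control group". The section also prints the Stata command, whose arguments are the two prevalences, an average number of children per school and the intracluster correlation.

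One allowance follows: "Considering a potential refusal to participate of 40%, 120 schools fulfilling the inclusion criteria will be invited to participate".

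Other sections describe how students enter and leave the analysis:

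- **Consent {26a}:** parents receive a form and "they need to sign it if they agree that their children participate in the study"; students are then asked for their own assent.
- **Discontinuation {11b}:** a student may leave the study, and that student's data are then not analysed.
- **Missing data {20c}:** missing answers are expected and are to be multiply imputed.
- **Objectives {7}:** use is compared just after the intervention and again four months later.
- **School eligibility {10}:** "Schools having at least two classes in the 6th and 7th grades".

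The Abstract carries the total forward as 8400 adolescents expected to be randomized.

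**The concern.** The 40% allowance protects the number of schools. It does nothing for the number of students analysed within each school, which is the other quantity that sets the power. The 4200 per arm appears to count every student on the roll of four classes per school, while the consent and withdrawal procedures mean that some of those students will contribute no data.

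If student loss is appreciable, the trial has less than the 80% power it declares, and 8400 is a count of eligible students rather than of students in the analysis. A null result would then be read as coming from a trial with 80% power for a 2-point reduction, although the plan does not support that figure once students are lost.

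**Working it through.** **Inputs, all from {14}:** two-sided alpha 0.05; power 0.80; control prevalence 0.0418; reduction 0.02, so intervention prevalence 0.0218; ICC 0.02. Students per school are 4200/35 = 120, which matches 2 grades x 2 classes x 30.

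**1. Reproducing the stated size**

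- Individually randomized size per arm (pooled variance under the null, normal approximation): n = [1.96 x sqrt(2 x 0.0318 x 0.9682) + 0.8416 x sqrt(0.0418 x 0.9582 + 0.0218 x 0.9782)]² / 0.02² = 1208 after rounding up.
- Design effect: 1 + (120 - 1) x 0.02 = 3.38.
- Per arm: 1208 x 3.38 = 4083; 4083/120 = 34.03 schools, rounded up to 35; 35 x 120 = 4200.

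The plan's figure reproduces. The unpooled formula gives 1204 x 3.38, about 4071, or 33.9 schools. A continuity correction (37 schools) and a cluster size of 30 (64 clusters) do not reproduce it.

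**2. What the 40% covers**

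70/0.6 = 117 schools, hence about 120 invited. The allowance is used up at school level.

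**3. Power with fewer analysed students per school**

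With m analysed students per school and equal school sizes, the effective size per arm is 35m / [1 + (m - 1) x 0.02]. The retained share is assumed, because the document gives no rate.

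| Retained share of 120 | m | Design effect | Effective n per arm | Power |
|---|---|---|---|---|
| 100% | 120 | 3.38 | 1243 | 81.1% |
| 95% | 114 | 3.26 | 1224 | 80.5% |
| about 91% | 109 | 3.16 | 1207 | 80.0% |
| 90% | 108 | 3.14 | 1204 | 79.9% |
| 80% | 96 | 2.90 | 1159 | 78.4% |
| 70% | 84 | 2.66 | 1105 | 76.4% |
| 60% | 72 | 2.42 | 1041 | 74.0% |

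Power falls slowly because losing students also lowers the design effect: at 60% retained, 40% of students are gone but the effective size falls only from 1243 to 1041, about 16%.

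**4. Unequal school sizes**

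The quoted command has no term for this. Using design effect = 1 + [(1 + CV²) x m - 1] x 0.02 at m = 120, with the CV assumed:

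- CV 0.2: design effect 3.476, effective n 1208, power 80.0%
- CV 0.3: design effect 3.596, effective n 1168, power 78.7%
- CV 0.4: design effect 3.764, effective n 1116, power 76.8%

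**5. A stricter reference**

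A t distribution on 68 degrees of freedom with unpooled variance gives 80.1% at the full 120 and 78.9% at 90% retained. The rounding slack almost vanishes on that basis, but the protocol's own figure comes from the normal approximation.

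**The case against.** A reader might infer that 80% power needs every student in every class to consent and be followed up. It does not. Rounding up to 35 schools leaves slack, and about 9% student loss is absorbed before power goes below 80%.

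A reader might also infer that the trial is shown to be underpowered. It is not. No consent, withdrawal or attrition rate appears in the document, and neither does a school-size CV, so every figure below 80% rests on an assumption.

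Three further points count in the plan's favour. The eligibility rule on classes is a minimum, so larger schools could offset losses: at 68% retained (80% consent x 85% follow-up, both assumed), six classes of 30 give 122 analysed per school and 81% power, and five give 102 and 79%. Adjustment for baseline scores might recover some precision. Multiple imputation is planned for missing answers.

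These points soften the concern without removing it. Section {14} fixes an average that equals four classes of 30 and does not count on larger schools. It claims no gain from baseline adjustment. Imputation cannot restore information from students who never consented. Nor is this a detail that an article would naturally leave to a fuller document: {14} sets out the calculation, its command and its one allowance, and that allowance is at school level.

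**Conclusion.** The point stands as a missing allowance, of moderate weight. The arithmetic in {14} is correct for 120 analysed students in each of 35 schools per arm. The stated 80% power and the 8400 total include no student-level loss, although consent, withdrawal and follow-up are all described elsewhere in the same protocol.

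On the plan's own inputs, 80% holds down to about 109 analysed per school. Beyond that, power would be about 78%, 76% and 74% at 80%, 70% and 60% retained. School-size variation alone would bring full-roll power to between 80% and 77% for a CV from 0.2 to 0.4. These figures assume the normal approximation, an ICC of 0.02 and 35 schools per arm; the retention figures also assume equal school sizes. The retention shares and CVs are illustrations, since the document supplies none. What can be said firmly is that the margin is about 9%, and that the protocol gives no reason to expect loss to stay within it.

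**What to change.** In {14}:

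- State the expected number of analysed students per school after consent, assent, withdrawal and follow-up. This should be the team's own estimate, for example from the 2019 pilot.
- State the expected variation in school size and include it in the design effect.
- Restate the power, or the difference detectable with 80% power, for 35 schools per arm at that number.
- Here and in the Abstract, describe 8400 as eligible students, not as students expected to be randomized or analysed.

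This is a rewritten paragraph and a changed label. The downside is a stated power that may be a few points less favourable. No extra schools are needed for an accurate statement.

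If the team prefers to keep 80%, the same formula with equal school sizes gives 37 schools per arm at 80% retained, 39 at 70% and 41 at 60%. The invitation list would then need review, since 120 invited at 40% refusal yields 72 schools, or 36 per arm.
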